#### Statistical analysis

The main analysis of primary and secondary endpoints will be based on the Intention-To-Treat principle, i.e. including all patients in the analysis who did not drop out within the first 4 weeks of the trial. In order to assess the clinical effect of the HeartMan intervention on the different outcomes, an additional per-protocol analysis will be performed in patients who adhere to the treatment plan for at least 50%. Based on these results, a dose-response analysis will be conducted to verify the relation between the level of adherence and intervention effects.

Prior to each analysis, distribution of the variables will be checked in order to choose correct statistical tests and identify outliers. In all analyses, *p* values < 0.05 will be considered to be statistically significant.

Effects of the proof-of-concept trial will be assessed by analysing baseline and end-of-investigation data between and among treatment groups. The primary endpoint of the HeartMan project is the self-reported improvement in HRQoL. First, T-tests or its non-parametric variant and chi-square tests will be used to compare the characteristics between the groups. Next, in order to assess the effect of the intervention among the different groups, a repeated measures design with time*group interaction effect will be chosen. A similar statistical approach will be performed for the secondary analyses.

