##### Sample size calculation

Sample size calculations were based on primary outcome data from the CHIRON project [13], showing that 90 patients are needed to show a difference of 5.8 beats per min in average daily awake heart rate– as a fundamental parameter correlating with HRQoL – with 90% power between the two groups. In order to account for possible drop-outs, the trial is performed enrolling 120 patients – 60 in each of the two participating countries – based on a 1:2 (control:intervention) randomization protocol.

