Following this assessment, patients are randomized to the intervention or control group according to a sealed randomization scheme with two balanced series of 60 envelopes (one for each country), each containing a random series of 20 control and 40 experimental numbers. In order to handle potential early drop-out of patients, a separate series of 24 sealed and balanced envelopes (12 for each country) is prepared.

Parallel to the baseline assessment, the following parameters are retrieved from the medical patient file as an additional base for providing personalized lifestyle advice: demographic and clinical characteristics, HF-related characteristics and laboratory parameters, risk factors, comorbidities, medication use and exercise capacity.

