### Handling missing data

A great effort will be made to have complete data on outcome measures and to use all obtained information. For early drop-out within 4 weeks after starting the intervention, novel candidates will be foreseen.

For those who drop out in a later phase, efforts will be made to perform the end-of-study examination and if not feasible, these will be considered as missing data. In the case of missing data, some of the outcome measures (e.g. heart rate or blood pressure) can be retrieved through data from the HeartMan system, using the Last Observation Carried Forward (LOCF) principle.

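### The main analysis is labelled intention-to-treat but leaves out randomised patients who drop out in the first 4 weeks, which can bias the comparison, plausibly in favour of HeartMan

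*Protocol article*

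**What the plan says.** - **Analysis set.** Under Statistical analysis, the main analysis of primary and secondary endpoints is said to follow the intention-to-treat principle, which is spelled out as "including all patients in the analysis who did not drop out within the first 4 weeks of the trial". The only other set described is per-protocol, requiring at least 50% adherence to the treatment plan.
- **Timing of randomisation.** Under Baseline visit: "Following this assessment, patients are randomized to the intervention or control group according to a sealed randomization scheme". Instruction in the use of the system comes later, at a home visit (Intervention).
- **Replacement.** Under Handling missing data: "For early drop-out within 4 weeks after starting the intervention, novel candidates will be foreseen". Under Baseline visit: "In order to handle potential early drop-out of patients, a separate series of 24 sealed and balanced envelopes (12 for each country) is prepared".
- **Follow-up after drop-out.** Under Handling missing data: "For those who drop out in a later phase, efforts will be made to perform the end-of-study examination". No such effort is stated for those who leave in the first 4 weeks.
- **Outcomes.** The primary endpoint rests on two self-reported questionnaires, the Self-care of Heart Failure Index (SCHFI) and the Minnesota Living with Heart Failure Questionnaire (MLHFQ). Both are collected at the start and end of the study.

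**The concern.** An intention-to-treat analysis keeps every randomised patient in the assigned arm. Here patients are removed after allocation because of something that happens after allocation, and the treatment itself can influence it. The label therefore promises a protection that the definition takes away.

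The two arms do not face the same early reasons for leaving. Only intervention patients receive the wristband, scale, blood pressure monitor, smartphone app and exercise programme. Patients necessarily know their arm. The Discussion itself names lack of adherence to technology as a plausible reason for mixed mHealth results, and calls the technology potentially challenging for elderly patients. If those who give up early would have scored worse, and more of them are in the intervention arm, the patients left in that arm look better than the arm as randomised. The per-protocol set is more selective still, so no described analysis would reveal this.

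The 4-week rule is also worded in two ways. Exclusion counts from the start of the trial, whereas replacement counts from the start of the intervention, which has no clear meaning for a control patient. Nothing says whether a death or a deterioration in this window counts as dropping out, so such patients could fall under the rule.

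**Working it through.** **Step 1. Are the excluded patients already randomised?** Yes. The order in the article is consent, baseline assessment, randomisation, then the home visit for the intervention arm. A patient who drops out during the first 4 weeks has therefore already been allocated.

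**Step 2. How many replacements are provided for?** There are 24 reserve envelopes.
- As a share of the planned 120: 24/120 = 20%.
- As a share of the possible total: 24/(120 + 24) = 24/144, or 1 in 6.

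This is the provision made, not a forecast of losses. The reserve series is described as balanced. If it follows 1:2 (an assumption), it holds 8 control and 16 intervention numbers, which is 8/40 = 20% and 16/80 = 20%. It therefore gives no evidence of one-sided loss.

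**Step 3. How large could the bias be?** The article gives no early drop-out rates by arm and no outcome difference between early leavers and stayers. Both are assumed below. Let p_I and p_C be the early drop-out shares in the intervention and control arms. Let D be the gap in mean outcome between stayers and early leavers, in SD units and the same in both arms. The mean among stayers exceeds the mean of the whole randomised arm by p × D, so

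bias = (p_I − p_C) × D.

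With 40 and 80 analysed after replacement,

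SE = √(1/40 + 1/80) = √0.0375 = 0.194 SD.

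With no true effect and a two-sided 5% test (the article states only p < 0.05; two-sided is assumed),

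type I error = 1 − Φ(1.96 − bias/SE) + Φ(−1.96 − bias/SE).

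| Early loss, intervention v control | Gap D (SD) | Bias (SD) | Bias/SE | Type I error | Of which favours HeartMan |
|---|---|---|---|---|---|
| 5% v 5% | any, equal in both arms | 0 | 0 | 5.0% | 2.5% |
| 15% v 5% | 0.5 | 0.05 | 0.26 | 5.8% | 4.4% |
| 20% v 5% | 0.5 | 0.075 | 0.39 | 6.7% | 5.8% |
| 20% v 5% | 1.0 | 0.15 | 0.77 | 12.1% | 11.8% |
| 20% v 0% | 1.0 | 0.20 | 1.03 | 17.8% | 17.7% |

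The last row needs 16 of 80 intervention patients lost, no control lost, and a full 1 SD deficit among those who leave. It marks the upper end of the range shown and is not an expected value.

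**Step 4. Do the two 4-week wordings agree?** They do not. The analysis rule can be applied to controls, because it refers to the trial. The replacement rule refers to the intervention, which controls never start. The baseline visit may take place up to 20 weeks before the trial starts, so randomisation, start of trial and start of intervention need not be the same date.

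**The case against.** The strongest reply is that the rule is stated openly and applies to both arms, and that the trial is a proof of concept whose results the authors themselves call preliminary. Controls may also leave early, for instance from disappointment. If loss is equal and equally selective there is no bias, and under moderate assumptions the inflation is small. All of this stands as a limit on size and direction. It does not justify the label or the absence of an all-randomised analysis, and the Discussion expects the results to serve as a basis for larger studies.

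Several stronger readings are tempting, but the article does not support them:

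- *The result is biased towards HeartMan.* No drop-out rates by arm are given, so this direction is plausible but not shown.
- *Replacement breaks the randomisation.* Replacements come from sealed, balanced envelopes and are themselves randomised. The harm comes from removing those already allocated.
- *The exclusion rule cannot be applied to controls.* The unclear clock belongs to the replacement rule only.
- *Early deaths are removed.* The article does not say so; the wording merely leaves it possible.
- *Replacement is unnecessary because 120 already allows for loss.* The article does say "In order to account for possible drop-outs, the trial is performed enrolling 120 patients", starting from 90. That figure is for a difference in heart rate, so it cannot show that numbers suffice for the questionnaire endpoints.

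It is also fair to say that keeping early drop-outs in the set without end-of-study data mostly turns exclusion into missing data. The gain depends on actually following them up.

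**Conclusion.** The point holds. The main analysis set is wrong as stated: it carries an intention-to-treat label while excluding randomised patients on a post-randomisation event, and no analysis of all randomised patients stands beside it. This can bias the main comparison, plausibly in favour of HeartMan. The effect on the type I error runs from none (equal, equally selective loss) through 5.8% to 12.1% for 15–20% intervention loss against 5% control loss, to about 18% in the extreme case. These figures rest on assumed drop-out rates and outcome gaps, a gap common to both arms, 40 and 80 patients analysed, and a two-sided test. The conclusion about the label and the missing analysis needs none of these assumptions. The two 4-week wordings also need to be reconciled.

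**What to change.** 1. Define the main analysis set as all randomised patients in their assigned arm, whenever they dropped out.
2. Extend the stated effort to obtain the end-of-study examination to early drop-outs in both arms, with the MLHFQ and SCHFI as the minimum.
3. Count any patients taken from the reserve envelopes as additional randomised patients, and keep the patients they follow in the analysis.
4. Report the 4-week set only as a modified intention-to-treat sensitivity analysis. Give it one starting date that applies to both arms, and state whether deaths and deterioration count as drop-out.

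The cost is more than a change of wording. Early drop-outs have to be followed up, and the end-of-study visit takes place in hospital. There will be more missing outcomes to handle by a prespecified method, because data retrieved from the HeartMan system do not supply questionnaire scores. The estimate may be somewhat diluted. The change is best made now: the trial was enrolling when the article was submitted, and end-of-study data that are not sought may not be recoverable later.

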### Intervention equipment

Participants randomized to the intervention group are equipped with a multi-monitoring health platform able to monitor, process and fuse physio-psychological and behavioural data. The main component of the trial equipment is the HeartMan wristband sensor developed by BITTIUM (Oulo, Finland). This is an ambulatory recorder and transmitter for heart rate, heart rate variability, galvanic skin response, skin temperature, respiration rate and motion. This wristband has Bluetooth communication, recording function, display, haptic interface and the ability to synchronize with other external devices. Apart from the HeartMan wristband sensor, the equipment consists of registered and commercially available devices including a digital bathroom scale (ADE, Model Silje BE1303), upper arm blood pressure monitor (A&D Medical, Model Number UA-611) and a pill box organizer (PuTwo, 7-Day AM/PM Night Reminder Medi-Planner). Furthermore, a smartphone (Nokia 6 TA_1021) with HeartMan app installed is provided for the duration of the trial.

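### The additional 50%-adherence analysis and the dose-response rest on post-randomisation, self-chosen adherence, so they can suggest a clinical effect of HeartMan where none exists

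*Protocol article*

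**What the plan says.** All of this is in the Protocol article; no separate SAP is shown. The Statistical analysis section first names an intention-to-treat-labelled analysis as the main analysis of primary and secondary endpoints, "including all patients in the analysis who did not drop out within the first 4 weeks of the trial". The adherence analysis is then introduced with a purpose of its own: "In order to assess the clinical effect of the HeartMan intervention on the different outcomes". The means chosen for that purpose is a restricted set of patients: "an additional per-protocol analysis will be performed in patients who adhere to the treatment plan for at least 50" per cent. On the basis of those results, "a dose-response analysis will be conducted to verify the relation between the level of adherence and intervention effects".

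One threshold serves every analysis: p "values < 0.05 will be considered to be statistically significant". The outcome is patient-reported: "The primary endpoint of the HeartMan project is the self-reported improvement in HRQoL". Group effects are tested as a time-by-group interaction on baseline and end-of-study data.

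On who has something to adhere to, the Intervention equipment section says "Participants randomized to the intervention group are equipped with a multi-monitoring health platform". Under Standard care, controls receive guideline treatment and education only.

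**The concern.** Adherence of at least 50% is observed after randomisation and decided by the patient. Because controls have no HeartMan plan, the natural reading of the per-protocol analysis is selected adherers against unselected controls. The section says only that the set consists of patients, so this is an inference, but the design leaves little else. Randomisation does not protect that comparison, nor a dose-response on the same variable.

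The mechanism that matters is a link between adherence and *change* that the app does not cause. A patient whose heart failure worsens may stop using the system and also report worse quality of life at the end. The article itself connects adherence with psychological state: Table 2 adapts communication to anxious, depressed or poorly motivated profiles to raise adherence.

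At stake is interpretation. The article attaches assessment of the clinical effect to the adherent subset and gives no exploratory label or caution. Its Discussion offers poor adherence as one plausible reason for mixed results in this field, and sees the results as a basis for larger studies. A favourable result in adherers could then carry weight that it has not earned.

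**Working it through.** **The plan's own figures.** The plan gives no adherence rate and no adherence–outcome correlation, so it has no figure of its own to reproduce on this point. Its sample size (90 patients, 5.8 beats per minute, "with 90% power between the two groups") states no SD. At 1:2 and two-sided 5%, it implies 5.8 / [√(1/30 + 1/60) × (1.960 + 1.282)] ≈ 8.0 beats per minute. Nothing below depends on it.

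**Inputs from the article.** 80 intervention and 40 control patients (Design); significance level 0.05 (Statistical analysis), taken as two-sided because sidedness is not stated.

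**Assumed inputs.** No true effect; a share *s* of the intervention arm reaches 50% adherence; adherence correlates ρ with the change score for reasons other than the intervention; normal distributions; everyone measured.

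**Step 1: bias in adherers versus all controls.** Bias in SD of change = ρ × φ(c)/s, where c is the cut-off on the standard normal scale that leaves a share *s* above it. For s = 0.6, φ(0.253)/0.6 = 0.644.

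**Step 2: rejection rate.** Adherers number 0.6 × 80 = 48. SE = √(1/40 + 1/48) = 0.214 SD. The rate is P(|Z + bias/SE| > 1.96).

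| ρ | Bias (SD) | Bias/SE | Two-sided rejection |
|---|---|---|---|
| 0 | 0 | 0 | 5% |
| 0.1 | 0.064 | 0.30 | 6.0% |
| 0.2 | 0.129 | 0.60 | 9.2% |
| 0.3 | 0.193 | 0.90 | 14.7% |
| 0.4 | 0.258 | 1.20 | 22.5% |

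A simulation of 5,000 null trials per setting gave 6.0%, 10.2%, 14.6% and 22.8% for ρ = 0.1 to 0.4. The comparison of the full arms stayed near 5%.

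**Step 3: sensitivity to the adherent share, at ρ = 0.3.** With 80% adherent (64 versus 40), the bias is 0.105 SD, SE = √(1/40 + 1/64) = 0.202, and rejection is about 8%. With 40% adherent (32 versus 40), the bias is 0.29 SD and simulated rejection is 23%.

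**Step 4: dose-response.** In the same simulation, the correlation of adherence with change among the 80 intervention patients was favourable at p < 0.05 in 15%, 44%, 78% and 96% of null trials for ρ = 0.1, 0.2, 0.3 and 0.4, against a nominal 2.5%. The association is real in those trials, but the intervention does not cause it.

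**Step 5: what cancels.** With two time points, the time-by-group interaction tests change. Assume a baseline-to-end correlation of 0.6, so the SD of change is √(2 − 2 × 0.6) = 0.894, and let adherence correlate r₀ with the baseline score and r₁ with the end score. Then ρ = (r₁ − r₀)/0.894. With 60% adherent:

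- r₀ = r₁ = 0.3: ρ = 0, no bias, 5% rejection.
- r₀ = 0.2, r₁ = 0.3: ρ = 0.11, 0.07 SD, about 6%.
- r₀ = 0.1, r₁ = 0.3: ρ = 0.22, 0.14 SD, about 10%.
- r₀ = 0, r₁ = 0.3: ρ = 0.34, 0.22 SD, about 17%.

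A stable advantage of fitter patients therefore drops out. Only differential change biases the result.

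**The case against.** The strongest reply is that the primary test is untouched. The intention-to-treat-labelled analysis is the main one, the adherence analysis is called additional, and a per-protocol analysis beside it is ordinary in a proof-of-concept trial that itself warns of preliminary results. That stands, and it limits the point to interpretation. A reader might infer that efficacy is to be demonstrated in adherers, or that a null main result would be overridden. The article says neither.

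A reader might also take the dose-response as a device for confirming efficacy. The sentence speaks of verifying a *relation* between adherence and intervention effects. That is loose wording for an association, not a claim of proof.

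A third tempting reading is that fitter, less depressed patients simply have better quality of life and so produce a false effect. Step 5 shows that this largely cancels in the planned test.

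The control set and the definition of adherence may be fixed in a fuller plan, so their absence from the article is not counted here.

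Finally, a complier-average estimate at a 50% cut-off assumes no effect below 50%. That is debatable for a graded behavioural programme, and if partial users benefit, the estimate is too large. It should therefore not be imposed as the sole replacement.

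What remains is that the stated purpose of the adherer analysis is to assess the clinical effect, and the analysis as described cannot do so without bias unless adherence is unrelated to change for other reasons.

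**Conclusion.** The point holds as a matter of interpretation and is worth correcting. It does not invalidate the main analysis. With 60% adherent and ρ from 0.1 to 0.4, a null intervention would appear 0.06 to 0.26 SD better, and a nominal 5% test would reject in 6% to 23% of trials. The rate is about 8% at ρ = 0.3 with 80% adherent, and nominal at ρ = 0. The dose-response is the more exposed of the two. Both ρ and the adherent share are assumptions, so the supportable statement is that these analyses *can* show benefit without a true effect, not that they will.

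**What to change.** 1. Rest the claim about HeartMan's effect on the comparison of all randomised patients. The current main set leaves out those who drop out in the first 4 weeks.
2. Where an effect of adhering is wanted, add a supportive complier-average estimate: randomised arm as instrument, adherence of at least 50% as exposure (zero in controls), adjusted for baseline score and country. State the assumption of no effect below 50%, and give a sensitivity analysis with adherence as a continuous exposure.
3. Report the at-least-50% comparison and the dose-response as exploratory associations, adjusted for baseline score, 6MWT, BDI-II and country. Detach the clinical-effect purpose from them.

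The cost is revised wording, a few lines of code and a wider interval. Under no true effect with 60% adherent and before covariate adjustment, the complier-average SE is about √(1/40 + 1/80)/0.6 = 0.194/0.6 = 0.32 SD, against 0.21 SD for the naive comparison, so the interval is roughly 1.5 times as wide. All the adjusting variables are already collected at baseline.

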### Handling missing data

A great effort will be made to have complete data on outcome measures and to use all obtained information. For early drop-out within 4 weeks after starting the intervention, novel candidates will be foreseen.

For those who drop out in a later phase, efforts will be made to perform the end-of-study examination and if not feasible, these will be considered as missing data. In the case of missing data, some of the outcome measures (e.g. heart rate or blood pressure) can be retrieved through data from the HeartMan system, using the Last Observation Carried Forward (LOCF) principle.

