#### Primary objective

The primary endpoint is the self-reported improvement in self-care and HRQoL, measured by the Self-care of Heart Failure Index [20] and Minnesota Living with Heart Failure Questionnaire [21]

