##### Baseline visit

After patients have signed the informed consent form stating their willingness to be randomized, a baseline assessment is planned in the hospital maximum 20 weeks prior to the start of the trial. During this visit, all patients perform a 6MWT, which is in line with the recommendations of the Heart Failure Association of the ESC [5] to evaluate one’s exercise capacity in case cardiopulmonary exercise testing (CPET) is not available.

In addition, every participant receives a self-administered questionnaire package which is filled in during the baseline assessment. These questionnaires have previously been described in the study outcome measures section and details are listed in Table 1*.*

**Table 1 Tab1:** Overview of the questionnaire package

Questionnaire	Description	Number of items	Subscales
Self – care of Heart Failure Index [20]	Self-care	22	Self-care behavior, self-care management, self-care confidence, and symptom perception
Minnesota Living with Heart Failure Questionnaire [21]	Health – related quality of life	21	Physical, socio-economic, and emotional/psychological aspects
Brief Illness Perception Questionnaire [24]	Illness perception	9	Cognitive representation, emotional representation, illness comprehensibility, and perceived cause of illness
Sexual Adjustment Scale [22] (subscale of the Psychosocial Adjustment Scale)	Sexual activity	6	Relationship and sexuality
Needs for Sexual Counseling Scale in Chronic Heart Failure [23]	Sexual activity	21	Symptoms, medication and information, relaxation, relationship, and psychological factors
State Trait Anxiety Inventory [26]	Anxiety	40	State anxiety scale (s-anxiety) and trait anxiety scale (t-anxiety)
Beck Depression Inventory II [27]	Depression	21	Depression and anxiety
Unified theory of acceptance and use of technology questionnaire [28]	User expectations and user experience	37	/
Self – composed questionnaire on nutritional behavior	Nutritional behavior	24	Drinking behavior and eating behavior
Self – composed questionnaire on nutritional knowledge	Nutritional knowledge	12 (14: patients with diabetes)	Knowledge about heart failure (and diabetes) nutrition

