##### Intervention

Instructions concerning the HeartMan intervention tool are given to the intervention group during a home visit.

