#### End-of-study visit

The intervention is terminated after using the system for three to six months. At this time, all participants from the intervention and control group undergo the end-of-study examination in the hospital that entails the same questionnaires and tests as during the baseline visit.

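### Late drop-outs lose their primary scores when the hospital examination is not feasible, although both primary questionnaires are self-administered and could be collected without a visit

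*Protocol article*

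**What the plan says.** The Handling missing data section of the protocol article covers patients who leave after the first four weeks: "efforts will be made to perform the end-of-study examination and if not feasible, these will be considered as missing data". The End-of-study visit section says that all participants "undergo the end-of-study examination in the hospital that entails the same questionnaires and tests as during the baseline visit". The baseline visit includes the six-minute walking test.

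The Primary objective section defines the primary endpoint by two questionnaires, the Self-care of Heart Failure Index and the Minnesota Living with Heart Failure Questionnaire. Both are in the Table 1 package, and the Baseline visit section says that "every participant receives a self-administered questionnaire package which is filled in during the baseline assessment". Outcomes are collected at start and end unless otherwise stated, and no interim assessment is stated for these two.

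One fallback is named: "some of the outcome measures (e.g. heart rate or blood pressure) can be retrieved through data from the HeartMan system", with last observation carried forward. On who has that system, the Intervention equipment section says "Participants randomized to the intervention group are equipped with a multi-monitoring health platform".

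The Statistical analysis section describes its intention-to-treat set as "including all patients in the analysis who did not drop out within the first 4 weeks of the trial". Late drop-outs therefore belong to it. The Handling missing data section also promises a great effort towards complete outcome data, but names no way to obtain questionnaires outside the visit.

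**The concern.** The rule makes availability of the primary endpoint depend on an event that the endpoint does not need. A patient who has returned the wristband, been admitted elsewhere or does not want to travel may still be able to fill in two forms. As printed, the rule goes from an infeasible examination straight to missing data. Such a patient has a baseline score and no later one, yet stays in the main analysis set.

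Two things are at stake. Precision is lost however the missing patients are distributed. The comparison of change between arms may also be biased, if the reason for loss is tied to how the patient's quality of life or self-care has changed and if the loss differs between arms. A difference is plausible: only the intervention arm has devices and an exercise programme to give up, and only that arm is said to receive a home visit ("Instructions concerning the HeartMan intervention tool are given to the intervention group during a home visit"). Plausible is as far as the documents go.

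**Working it through.** **Inputs from the article.** 120 patients, 80 intervention and 40 control (Design); 90 needed and 120 enrolled to allow for drop-out, 90% power (Sample size calculation); significance at p < 0.05 and a time-by-group interaction on baseline and end data (Statistical analysis). Sidedness is not stated; two-sided is assumed.

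**The plan's own figure.** The 90 patients are for a heart-rate difference of 5.8 beats per minute and no SD is given, so 90 cannot be reproduced outright. Solving backwards at 30:60, SD = 5.8 / [(1.960 + 1.282) × √(1/30 + 1/60)] = 8.0, a standardised difference of 0.725. This concerns heart rate, not the questionnaires, and serves only as a yardstick. The allowance for loss is 1 − 90/120 = 25%, or 30 patients.

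**Precision.** Take SE in SD units as √(1/n_I + 1/n_C), counting only patients with an end score.
- All 120: √(1/80 + 1/40) = 0.194.
- 25% lost evenly (60 and 30): √(1/60 + 1/30) = 0.224, which is 0.224/0.194 = 1.15 times as large.
- Half of those recovered (70 and 35): √(1/70 + 1/35) = 0.207, or 1.07 times.

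The full 25% is an upper illustration, since some of the allowance may be used by early drop-outs.

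**Bias.** Within an arm, let m be the share missing and d the amount, in SD of change, by which completers' change is more favourable than that of the missing. The full mean is (1 − m) × observed + m × missing, so the observed mean is too favourable by m × d. The arm contrast is shifted by m_I × d_I − m_C × d_C. The analysis tests change, so d must be a difference in change; a patient who was already poor at baseline does not enter through level alone. All values of m and d below are assumptions. Type I error is two-sided, by normal approximation with SE = √(1/[80(1 − m_I)] + 1/[40(1 − m_C)]).

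- 25% and 25%, equal d: 0.25d − 0.25d = 0; type I error 0.05.
- 25% and 25%, d_I = 1, d_C = 0.5: 0.25 − 0.125 = +0.125 SD; 0.086. With the two d values exchanged, −0.125 SD; 0.086.
- 15% intervention, 5% control, d = 0.8: 0.8 × 0.10 = +0.08 SD. With shares reversed, −0.08 SD.
- 30% and 15%: d = 0.5 gives +0.075 SD (0.064); d = 1 gives +0.15 SD (0.106).
- 15% and 30%: d = 0.5 gives −0.075 SD (0.063); d = 1 gives −0.15 SD (0.102).

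Against the yardstick, 0.08/0.725 = 11% and 0.15/0.725 = 21%.

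**After the change.** If remote forms recovered half of those lost in each arm, and the rest had the same d, the 30%/15% case becomes 15%/7.5%. With d = 1, bias is 1 × 0.075 = 0.075 SD and type I error 0.066. With d = 0.5, bias is 0.5 × 0.075 = 0.0375 SD and type I error 0.054.

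**The case against.** The strongest reply is that this is a condensed article. It does not forbid completion by post or telephone, the full protocol may provide for it, and the opening promise of a great effort and of using all information obtained could cover a returned form. Nor does the text say that a failed walking test voids a completed questionnaire, or that the examination must be complete to count. The device fallback is introduced with examples and is not limited to heart rate and blood pressure. All of that is fair. What stands is that the article states a rule for this exact case, and the rule ends in missing data without an intermediate step. However the examples are read, none of the listed devices records the two primary scores.

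A reader might infer more: that patients too ill to travel are the ones lost, so that the comparison favours the well. The documents do not support this. They give no reasons for infeasibility. Even illness-driven loss only makes the completers healthier; the arm contrast stays unbiased if amount and kind of loss are equal, and its sign is open otherwise.

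It would also be too strong to say that no analysis can help. A likelihood-based repeated-measures model can use baseline scores and is valid if loss depends only on observed data. It does not help where loss depends on the unseen change.

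Finally, telephone collection turns a self-administered form into an interview, so mode may become related to illness or arm. That is a real cost and the reason to prefer post.

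**Conclusion.** The point holds as a cheap improvement to follow-up; bias is not demonstrated. As printed, the rule can discard primary scores that could be obtained from patients in the main analysis set, and the named rescue does not reach those scores in either arm. Loss of precision follows from any such loss: an SE up to about 15% larger if the whole 25% allowance were lost late and evenly. Bias in the time-by-group comparison is conditional on loss that is related to change and differs between arms. The illustrations run from 0 to about 0.15 SD in either direction, with 0.08 SD for 15% against 5% and d = 0.8. They rest on assumed missing shares and assumed differences in change, and should not be read as estimates for this trial.

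**What to change.** Amend the Handling missing data section as follows.

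- When the hospital examination is not feasible or is declined, and consent to data collection has not been withdrawn, collect the Minnesota questionnaire and the Self-care of Heart Failure Index at the patient's scheduled end-of-study date, in both arms alike.
- Send them by post as self-administered forms first; use the telephone only as a last resort.
- Record the mode of completion and the reason for non-attendance, by arm.
- Distinguish stopping use of HeartMan from withdrawing from data collection.
- Class the primary endpoint as missing only if this also fails.

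The article gives the intervention period both as six months and as three to six months; these passages need reconciling so that the scheduled date is defined.

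The cost is protocol wording and a small number of mailed forms or calls for 22 + 21 = 43 items. The downside is that a few scores come from another mode of administration. A sensitivity analysis can examine this, though with few patients. Deaths and withdrawn consent are not recovered. Recruitment was still open when the article was submitted, and scores that are never collected cannot be restored later, so the change is worth making early.
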